## Quantitative study

Within the quantitative study we will aim to:

1. Undertake a propensity score matched (PSM) cohort study to examine the individual level changes in recidivism and re-offending of DVA perpetrators.2. Examine the population level effects in the incidence of DVA following the introduction of CARA.

### Population, intervention, comparison and outcome

A previously published study examining the impact of the CARA was undertaken across the West Midlands (
University of Birmingham, 2021). As part of that project a PSM cohort approach was chosen to disentangle the treatment effects from confounding variables which may exist in this study (
Figure 1). However, as this study was only undertaken in one locality it was not sufficiently powered nor contained a diverse enough population to examine whether changes in recidivism or reoffending differed per offender sub-groups in the population such as by age, sex, ethnicity or socio-economic group. Undertaking such an evaluation of these sub-groups would be invaluable in providing further insight into specific groups of offenders who may respond better or worse to the CARA intervention. In this study, we will be able to do this as we are undertaking a nation-wide study to examine the effects of the interventions. Further details on the PSM cohort approach are below:

**Figure 1. f1:**
[figure not shown]
Hypothesis 1: Completion of the CARA conditional caution leads to a reduction in incidence and/or severity of DVA at the population level.

**
*Data source*
**: Data held on the police Record Management System (RMS) database, or equivalent, will be extracted, pseudonymised and shared in aggregated form.

**
*Population*
**: The population sample to be included in the analysis are those that are eligible for the CARA intervention.

**
*Intervention*
**: Those who have undertaken the CARA intervention will form the intervention group. CARA is a conditional diversionary caution offered by the police to first time adult offenders of DVA of standard risk or medium risk (in some areas). Offenders are required to undertake two mandatory workshops that increase awareness of their abusive behaviour and the safety of partners and children. In contrast to restorative justice, CARA is an awareness raising intervention for offenders, that utilises a trauma informed approach and motivational interviewing techniques across the pair of workshops. In these workshops offenders are further signposted onto services that support improvements in the wider determinants of their offending behaviour, such as to their GP, drug and alcohol services or onto a community perpetrator programme.

**
*Comparison*
**: Using PSM approaches a comparator group will be formed from those who meet the eligibility criteria for CARA but are based in an area that is currently not delivering the CARA intervention. Covariates for the matching will include demographics, such as age, gender, ethnicity, whether in same sex relationship; offending behaviour/wider determinants, such as offending history and/or risk profile, mental health, employment status, alcohol misuse, accommodation type and; wider contextual factors, such engagement with other perpetrator interventions.

**
*Outcome measures*
**: The primary outcome will be DVA
reoffending within 12 months. The primary outcome will be described as either i) number of DVA arrests ii) number of DVA crimes. The secondary outcome(s) will include for example total number of arrests, crime severity score, total number of offences.

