## Aims and objectives

Using a pragmatic concurrent mixed methods design the aim of our study is to evaluate Project CARA following its wider rollout nationally. By using this approach to mixed method study design, both methods will be conducted and analysed independently before findings are later integrated together (
Creswell & Plano Clark, 2018).

Our research objectives are to:

Understand the perceptions and experiences of clients, partners/former partners and professionals involved in the delivery of Project CARA.Examine whether the completion of the CARA conditional caution leads to a reduction in the incidence and/or severity of DVA at the population level.Develop an overarching logic model for Project CARA in order to understand the mechanisms of action of intervention components and anticipated outcomes (all phases).Explore the wider contextual factors around offending behaviour and answer research questions around the implementation of CARA including, for example, the types of violence that result in a CARA caution.Analyse the cost-benefits of Project CARA in comparison with a matched cohort who do not receive Project CARA.

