### Analysis of quantitative data

**
*Interrupted time series*
**. Using interrupted time series (ITS), we will also examine whether the introduction of the CARA conditional caution leads to a hypothesised population-based reduction in the incidence of DVA, as hypothesised in Figure 2. A secondary outcome will be to assess if there was a change in the severity of recorded DVA before and after the introduction of CARA.

 As an intervention study design, ITS is a valuable study design compared to traditional observational study designs (such as cohort or case control studies) particularly when there is a need for retrospective evaluations which have already been implemented, either without randomization or to a whole population, both of which are applicable in the CARA intervention (
Bernal *et al.*, 2017). By nature, ITS can be applied to natural experiments when an intervention is introduced at the population level at a clearly defined period of time and involves observing a single population over time.

In an ITS study, a time series of the outcome of interest (incidence of domestic violence and abuse) is used to establish an underlying trend, which is ‘interrupted’ by an intervention (e.g. CARA being offered in a force area) at a known point in time. The pre-intervention underlying trend is compared with the post-intervention period to identify whether the intervention is associated with any changes in outcome.

Initially summary statistics and plots will be undertaken, including a scatter plot of the time series demonstrating before and after comparisons of the incidence of DVA across the force areas. These will include sub-analyses, by age, gender, ethnicity, force area and whether in same sex relationship.

Following this a segmented regression model such as the one below will be constructed to undertake the ITS model:

Yt-=α+β1Tt+β2Xt+β3XtTt

Yt is the aggregated outcome variable measured at each equally-spaced time point (month)

Tt is time

Xt is study phase

XtTt is time after interruption

α, β1, β2 and β3 are model parameters

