As our outcome measure (DVA occurrences) are count data, we will also undertake a Poisson model. Calendar quarters will be included as a categorical variable to account for seasonality. The final model will provide a measure of relative risk with 95% confidence intervals to describe the change in incidence in DVA across the CARA sites before and after the introduction of the intervention. We will account for covariates of interest in the final model to examine any changes specific to offender subgroups of interest, including age, sex, ethnicity and socioeconomic status. Confounding events or co-interventions that will affect study outcome will be explored through consultation with the research team, including all stakeholders, and through the qualitative research. Time varying confounders might include, for example, lockdowns from the COVID-19 pandemic.

Where possible we will also aim to undertake a controlled interrupted time series (CITS) (
Bernal *et al.*, 2018). In this case the control data will be derived from sites where CARA was not delivered during the study timeframe. The CITS model can be described as:

Yt-=α+β1Tt+β2Xt+β3XtTt+β4Zt+β5ZtTt+β6ZtXt+β7ZtXtTt

Yt is the aggregated outcome variable measured at each equally-spaced time point (month)

Tt is time

Xt is study phase

XtTt is time after interruption

Zt is treatment or control group

ZtTt is time for treatment and 0 for control,

ZtXt is study phase for treatment and 0 for control,

ZtXtTt is time after interruption for treatment and 0 for control

α, β1, β2 , β3 β4, β5, β6 and β7 are model parameters

**
*Geomapping*
**. We will also undertake geomapping using postcode data from regional and national data (either from the address where the incident took place or the perpetrator’s address). The postcode data will be input using googlemaps to generate a visual-coloured map. The visuals produced through this method are not accurate enough to render an individual’s home address to become identifiable; postcodes are replaced with colour patches, similar to heat maps, covering a large area. The postcodes entered into google through this process are not stored by google and therefore no data will be stored and shared through this method.

**
*Health economics analysis*

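### Hypothesis 1 and the second objective can be met by a fall in severity alone, although the population-level analysis rests on incidence and ranks severity as secondary

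*Protocol article*

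**What the plan says.** The protocol article states the population-level question in several places, and they do not agree on whether severity counts.

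**Where incidence or severity would do**
- *Population, intervention, comparison and outcome*, Hypothesis 1 (with Figure 1): "Completion of the CARA conditional caution leads to a reduction in incidence and/or severity of DVA at the population level".
- *Aims and objectives*, second objective: to examine whether completing the caution "leads to a reduction in the incidence and/or severity of DVA at the population level". The two outcomes are not ranked.

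**Where incidence is the outcome and severity is absent or secondary**
- *Quantitative study*, second aim: "Examine the population level effects in the incidence of DVA following the introduction of CARA". Severity is not mentioned.
- *Analysis of quantitative data*, interrupted time series: whether introducing CARA "leads to a hypothesised population-based reduction in the incidence of DVA, as hypothesised in Figure 2".
- The same paragraph: "A secondary outcome will be to assess if there was a change in the severity of recorded DVA before and after the introduction of CARA".
- *Analysis of quantitative data*, Poisson model: "The final model will provide a measure of relative risk with 95% confidence intervals to describe the change in incidence in DVA". No model or interval is described for severity.
- *Strengths and limitations of this study*: the purpose given for the time series is again a reduction in incidence.
- For the matched cohort, crime severity is also ranked below the primary outcome: "The secondary outcome(s) will include for example total number of arrests, crime severity score, total number of offences".

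**The concern.** A hypothesis joined by and/or is satisfied by either part. Read literally, Hypothesis 1 holds if severity falls while incidence stays level or rises. The analysis section treats incidence as the effect under test and severity as supporting information. A reader of the final report could not tell from the protocol whether a severity-only result confirms the hypothesis or is a secondary observation beside a failed one.

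The two outcomes can plausibly part company. The Introduction says that recorded figures probably understate DVA considerably. If severity were analysed as an average per recorded incident (an assumption; the article does not say), fuller recording of minor incidents would push incidence up and average severity down. The and/or wording would count that as success.

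The stakes are practical. The Dissemination plan expects the evidence to bear on commissioning and possibly on legislation about conditional cautions. What counts as a population-level success should be fixed before the results are known.

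**Working it through.** **Step 1. Outcome patterns under the two sets of wording.**

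| Incidence | Severity | Hypothesis 1 and second objective as worded | Aim and time series ranking |
|---|---|---|---|
| falls | falls | met | hypothesised effect seen; secondary outcome agrees |
| falls | no fall | met | hypothesised effect seen |
| no change or rises | falls | **met** | **hypothesised effect not seen; secondary finding only** |
| no change or rises | no fall | not met | not seen |

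The passages disagree in the third row only. In that row the stated hypothesis and the stated analysis lead to opposite conclusions.

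**Step 2. Effect on false claims.** The article gives no alpha, power or familywise rate, so there is no figure of its own to reproduce. The calculation below needs three inputs:
- The direction is a reduction, from Hypothesis 1.
- Each outcome is judged by a 95% interval. The article gives one for the incidence relative risk; extending it to severity is an assumption. A false reduction then occurs with probability 0.025 per outcome.
- The correlation r between the two test statistics is not given, so a range is used.

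With no true effect on either outcome:
- Incidence alone: 0.025.
- Either outcome, independent: 1 − (1 − 0.025)² = 1 − 0.950625 = 0.0494.
- Either outcome, correlated: 1 − Φ₂(1.96, 1.96; r), where Φ₂ is the bivariate normal distribution function.
- Upper bound at any correlation: 0.025 + 0.025 = 0.05.

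| r | Chance of a false claim of reduction | Multiple of 0.025 |
|---|---|---|
| 0 | 0.0494 | 1.98 |
| 0.3 | 0.0476 | 1.90 |
| 0.5 | 0.0454 | 1.82 |
| 0.7 | 0.0417 | 1.67 |
| 0.9 | 0.0352 | 1.41 |
| 0.99 | 0.0283 | 1.13 |

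If r were negative, as in the recording scenario above, the rate would lie between 0.0494 and the bound of 0.05.

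**Step 3. After the fix.** If incidence alone decides Hypothesis 1, the chance of a false claim of reduction returns to 0.025 under the same assumptions.

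**The case against.** The strongest reply is that the ranking is already visible. Incidence alone is the second quantitative aim, the time series outcome, the quantity the final model estimates and the purpose given under Strengths and limitations. Severity is labelled secondary in both designs. A broad objective that covers a primary and a secondary outcome is ordinary drafting, the objective is only to examine a question, and no formal success rule is stated. Both figures are also missing from the text at hand. Hypothesis 1 stands with Figure 1, which the article cites when describing the matched cohort, whereas the time series points to Figure 2.

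Much of this stands, and it limits the point:
- A reader might infer that a 5% error rate is breached. The article sets no such rate, and on the hypothesis's own directional wording the chance of a false reduction stays at or below 5%. A two-sided calculation, 1 − 0.95² = 9.75% if independent, would count significant rises as successes, which Hypothesis 1 does not.
- A reader might infer that Hypothesis 1 is the study's only hypothesis. It is the only numbered hypothesis shown; the time series refers to another, on incidence, in Figure 2.
- A reader might object that no alpha split or testing order is given. That commonly belongs in the analysis plan, which is not shown, so its absence here is no fault.

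The reply does not remove the conflict in the text. Hypothesis 1 is explicitly about the population level, which is the level of the time series, and severity is secondary in the cohort as well. Under whichever analysis it is placed, its wording gives severity a role that the outcome ranking denies. The reference to an incidence hypothesis in Figure 2 sharpens this, because two statements of the population-level hypothesis then differ on whether severity counts. An unseen analysis plan would not change the protocol's own hypothesis and objective.

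**Conclusion.** The point holds as an inconsistency over what counts as success. Hypothesis 1 and the second objective accept a reduction in severity alone; the population-level aim and the time series rest on incidence, with severity secondary. A null or adverse incidence result with a fall in severity could therefore be reported as confirming Hypothesis 1.

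The error-rate effect is modest and conditional. If each outcome is judged by its own 95% interval and neither truly changes, the chance of a false claim of reduction goes from 2.5% to about 4.9% (independent) or 3.5% (correlation 0.9), with a ceiling of 5%. The severity interval and the correlations are assumptions. The documents do not support a claim that a stated error rate is exceeded. The case for correction rests mainly on the conflicting conclusions in the third row of the first table, which need no assumption about testing.

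**What to change.** Reword Hypothesis 1 and the second objective to match the second quantitative aim and the time series:
- Hypothesis 1 is a reduction in the incidence of DVA at the population level, decided by incidence.
- Severity becomes a separate secondary hypothesis, with a statement that it cannot by itself confirm Hypothesis 1.

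Testing severity formally only after incidence has succeeded would be compatible with this, but is optional.

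The cost is wording in two places, with no change to data or models. The one loss is that a severity-only effect could no longer be claimed as confirming Hypothesis 1; it would still be reported as a secondary result, as the time series section already implies.

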## Ethics and governance

Research ethical approval has been sought from the University of Southampton (Higher Education Institute) Ethical Committee and approved on the on the 1
^st^ June 2022 (Ref: ERGO ID: 71818.A1) As this research study is not being conducted within prisons nor within the national health service, neither HM Prison and Probation Service or Health Research Authority approval will be needed, respectively. Upholding ethics, good governance and quality in practice is central to all processes. The project will also comply fully with the ESRC's Research Ethics Framework, The Offender Health Research Network and GDPR. This includes upholding the ethical research governance in line with the Ethics Policy Statement at the University of Southampton
https://www.southampton.ac.uk/about/governance/policies/ethics.page.

There are a number of central tenets that should be maintained throughout the research. These include the moral principles guided by four main principles of bioethics (
Beauchamp & Childress, 2013). The principles are autonomy (informed consent), non-maleficence (do no harm), positive beneficence (benefits of research outweigh the risks) and justice (research strategies and procedures are just and fair).

Police data will be shared as anonymised, aggregated form. Information sharing agreements have been developed and have been signed by the majority of force areas. No additional permissions are required to access this routine data. The lead researcher handling police data will undertake national police vetting with Warwickshire police in order to handle police data. Each police force will be required to develop, regularly review and sign a Data Protection Impact Assessment (DPIA) for the project.

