**. The aim of the health economic analysis will be to examine the cost-benefits of Project CARA with matched controls. Relevant benefits will include incidents of reoffending and quality adjusted life years (QALYs) obtained from the published literature. Cost considerations will include the cost of delivering Project CARA, including mobilisation and ongoing delivery costs and for both groups we will examine lost economic output, health, legal, social and specialist resources and any personal resource consequences (for example damages, divorce). The perspective of the analysis will include health and social care, criminal and legal and specialist services in the first instance and will explore the inclusion of costs to the victim in a wider cost perspective.

Data sources will include the CARA victim contact form, Crime Survey for England and Wales, and information collected from police taking part in the project. Unit costs will be taken from relevant sources such as the Home Office or Department of Health and Social Care. Results will be presented in a cost-benefit analysis as incremental costs per reoffence avoided and incremental costs per QALY. Probabilistic sensitivity analysis (PSA) will be used to allow for uncertainty around cost and effectiveness estimates.
*
**
**
*

**
*Routine service data*
**. Routine data from the main third sector implementing agencies will be used to examine the fidelity, dose and reach of the CARA intervention. Routine data sources may include, for example, video observations of group work, referral forms and outcome questionnaires. These will be summarised descriptively. All quantitative data sources will be aggregated.

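### Police data are described as shared in aggregated form, which does not fit a propensity score matched cohort of individual offenders

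*Protocol article*

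**What the plan says.** Three places in the protocol article describe the form of the data.

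- **Population, intervention, comparison and outcome, Data source item:** "Data held on the police Record Management System (RMS) database, or equivalent, will be extracted, pseudonymised and shared in aggregated form". This is the first of the details announced for the matched cohort.
- **Ethics and governance:** "Police data will be shared as anonymised, aggregated form".
- **Analysis of quantitative data, end of the Routine service data paragraph:** "All quantitative data sources will be aggregated".

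The analysis these data must support is quantitative aim 1: "Undertake a propensity score matched (PSM) cohort study to examine the individual level changes in recidivism and re-offending of DVA perpetrators". On the comparison group the article says: "Using PSM approaches a comparator group will be formed from those who meet the eligibility criteria for CARA", and places those people in areas not delivering CARA. The matching covariates include "demographics, such as age, gender, ethnicity, whether in same sex relationship" and "offending history and/or risk profile, mental health, employment status, alcohol misuse, accommodation type", plus engagement with other perpetrator interventions. The primary outcome is DVA reoffending within 12 months, expressed as a number of DVA arrests or of DVA crimes.

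Aim 2, the interrupted time series and its controlled version, is defined on a monthly aggregated outcome.

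**The concern.** A propensity score is a model for each person's probability of being in the intervention group given that person's covariates. Fitting it, matching on it, checking balance and comparing outcomes in the matched set all require the covariates, the exposure and the later offences to be tied to the same offender. A data set already reduced to totals has lost that link. Because the comparators come from other areas, a CARA force cannot repair this by matching within its own records before it aggregates.

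If the aggregation rule is applied literally, aim 1 loses its data. With it go three things:

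- the primary outcome as defined for the matched cohort;
- the offender-subgroup analysis of the cohort, which the article presents as its advance over the earlier single-locality study;
- the economic comparison with matched controls (the last objective in Aims and objectives, and the Health economics analysis paragraph).

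If the rule is not meant literally, the governance description of what the forces will release is inaccurate. Either way the text needs correcting.

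**Working it through.** The article gives no sample size or power for the quantitative study, so there is no stated figure to reproduce. The check compares what each analysis needs with what the stated data form supplies, and then asks whether finer tables could stand in for records.

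**Step 1. Need against supply**

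| Analysis | Unit needed | Do ordinary aggregates supply it? |
|---|---|---|
| Matched cohort: score, matching, balance | Offender, with joint covariates and exposure | No |
| Primary outcome in the cohort | Offences over 12 months, linked to the index offender | No |
| Subgroups of the matched cohort | As above | No |
| Cost-benefit against matched controls | Reoffending and resource use by matched group | No, because the groups come from the match |
| Interrupted time series, controlled or not | Monthly counts by area | Yes |
| Subgroups within the time series | Monthly counts stratified by age, sex, ethnicity and so on | Yes |

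Force-level totals would not do either. The abstract expects quantitative data from up to nine police forces, so that analysis would have at most nine CARA units. It would compare areas, not individuals.

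**Step 2. Could cross-tabulated aggregates replace records?**

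Covariates listed in the Comparison item: 4 demographic + 5 on offending and wider determinants (offending history and risk profile counted as one) + 1 contextual = 10. The list is introduced as examples, so ten is approximate.

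Number of strata = product of the number of levels of each covariate. The article gives no levels, so these are assumptions:

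- *Minimum, two levels each:* 2^10 = 1,024 strata; by intervention status, 2 × 1,024 = 2,048.
- *Age 5, ethnicity 5, employment 3, accommodation 4, the other six 2 each:* 5 × 5 × 3 × 4 × 2^6 = 19,200; by intervention status, 38,400.
- *As above, but offending history/risk with 3 levels:* 5 × 5 × 3 × 3 × 4 × 2^5 = 28,800; by intervention status, 57,600.

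Each table must then be split again by the number of arrests or crimes. A complete table of this kind is mathematically equivalent to categorised records, so matching from it is possible in principle. But it is then record-level data in all but name, and could hardly be called anonymised and aggregated. How sparse the cells would be cannot be calculated, because no cohort size is given.

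**Step 3. Is another route provided?**

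The article mentions no record-level transfer to the research team, no matching carried out inside forces and no distributed method.

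**Step 4. Are the governance statements consistent with each other?**

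The Data source item says pseudonymised; Ethics and governance says anonymised. These are different statuses for the same police data. Pseudonymisation is applied to person-level records and has little meaning for a table of counts.

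**The case against.** The strongest reply is that this is loose wording. Pseudonymising implies person-level records at some stage. Police vetting of the researcher who handles the data, and a DPIA from every force, also fit record-level access better than anonymous totals. Aggregated may mean pooled across forces, or aggregated for reporting. A condensed article may also leave the data flow to the full protocol.

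Much of this stands as a statement of probable intent, and it is why the point is framed as a contradiction to reconcile. It does not remove the point. The sentence that says pseudonymised also says the data are shared in aggregated form, and Ethics and governance says anonymised. The article states a rule here, and the rule conflicts with aim 1; it is not a detail left for elsewhere.

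Two narrower objections also stand. The sentence on all quantitative data sources closes a paragraph about third-sector agencies' routine data, so it is weaker evidence for the police extract; the other two statements are enough without it. And a distributed or staged matching method could in principle work without sharing records, but none is described.

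**Conclusion.** The concern holds as an internal contradiction with practical consequences. Under the stated data form, the propensity score matched cohort, its subgroup analyses and the matched cost-benefit comparison could not practically be run. The time series analyses are unaffected. The conclusion rests on the ordinary meaning of aggregated and on the absence of any stated alternative route. It does not depend on the assumed covariate levels, which only show that cross-tabulation is no real escape (1,024 strata at the minimum, 19,200 to 28,800 under the richer assumptions, before any split by intervention or outcome).

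A reader might infer more than the article supports:

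- *That aim 1 is certain to fail.* The data actually to be supplied cannot be seen, and record-level data may be intended.
- *That the sharing agreements lock in unusable data.* Their content is not shown.
- *That all subgroup work is lost.* Subgroups in the time series can be run on stratified counts.
- *That geomapping breaks the same rule.* The article describes "geomapping using postcode data from regional and national data"; it does not say that this is the shared police extract, and counts by postcode are themselves aggregates.

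**What to change.** Reconcile the Data source item, Ethics and governance, and the closing sentence of Routine service data with aim 1 by taking one of two routes:

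1. State that the matched cohort uses a pseudonymised record-level extract: one row per eligible offender, with a pseudonymous identifier, index date, pre-index covariates, and dated DVA arrests and crimes over 12 months.
2. Specify a distributed matching method that works across CARA and non-CARA forces without sharing records.

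In either case, use one term (pseudonymised or anonymised) for each data set and keep monthly aggregates for the time series. Under the first route, say that a force able to supply only aggregates contributes to the time series and not to the matched cohort. Check that the information sharing agreements, DPIAs and ethics description match the chosen route.

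The wording change is small. The possible cost lies in governance: the majority of force areas have already signed agreements, and those agreements and the ethics description may need amendment if they follow the aggregated wording. If they already provide for record-level data, only the article's text has to change. Settling this before the remaining agreements and DPIAs are signed keeps the cost down.
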